### Phase 1: establishing an evaluation framework

#### Aim and methods

We aim to contribute to a scientifically sound, comprehensive evaluation framework for PPI in health services research in Germany based on a logic model.^56^ It will be used to describe the causal processes through which PPI produces outcomes and impacts. Information on meaningful and successful PPI in health services research from the perspective of researchers and patients will be gathered by conducting a web-based survey and focus group interviews. Results will be presented in a co-design workshop to establish an evaluation framework (see figure 1).

##### Web-based survey

The web-based survey consists of different modules for researchers and patients. They will be recruited through several time-shifted strategies: (a) Identification and invitation of principal investigators of publicly funded health services research, (b) Identification and invitation of researchers and patients (or their representatives) involved in publicly funded health services research that implements PPI and (c) Through personal knowledge (eg, DNVF), including its patient advisory board).

#### Recruitment and procedures

Principal investigators of publicly funded projects in the field of health services research (German Research Foundation (Deutsche Forschungsgemeinschaft, DFG), Federal Ministry of Research, Technology and Space (Bundesministerium für Forschung, Technologie und Raumfahrt, BMFTR), Federal Ministry of Health (Bundesministerium für Gesundheit, BMG), innovation fund of The Federal Joint Committee (Gemeinsamer Bundesausschuss, G-BA) can be identified using databases (eg, funded projects information system (GEPRIS), funding catalogue of the BMFTR). The inclusion criteria specify that the project must be conducted in Germany, initiated in 2010 or later, and aimed to gain knowledge about healthcare. In the GEPRIS Database, 78 researchers are currently listed, while the BMBF funding catalogue contains 571 projects. Researchers will be contacted via email and invited to participate in a linked web-based survey. With regard to sampling strategy 2, these principal investigators can name further researchers and patients for participation in the survey. Four weeks after the second reminder email has been sent to the principal investigators, sampling strategies (b) and (c) will be applied. Links to the web-based survey will be sent via email. Two reminders will be sent.^57^ The web application Research electronic data capture (REDCap) will be used to implement the web-based survey.^58^ Informed consent will be obtained online.

In module B, all participating principal investigators and researchers and patients will provide information on individual characteristics. Researchers will answer questions on age, gender, seniority^19^ and patients will be asked questions with regard to age, gender, health condition with lived experience and membership of self-help organisation. In module C, the participants are presented with information on PPI and will be asked to rate different elements of the frameworks for supporting PPI in research according to their relevance.^11 38–41^ For both aspects, a nine-point Likert scale (1=not relevant; 9=very relevant) will be used. In addition, open-ended questions will be asked about whether any relevant aspects are missing. At the end of the web-based survey, participants can consent to be contacted for further interviews or surveys in the project, which requires storing their email address and further details (such as project and investigator characteristics) in a project database and/or for receiving information about the project results.

#### Data analysis

To analyse the project and participant characteristics, we will calculate the median, mean and SD for the interval data and frequencies for the nominal items. In the analysis of the ratings (module C), the median, mean and SD will be calculated. All data will be analysed using IBM SPSS Statistics 29.^59^ The descriptive analysis of the web survey is intended to provide an overview of the relevant domains of internationally developed PPI frameworks from the perspective of health services researchers in Germany.

##### Focus groups

Focus groups^60^ will be conducted to validate and expand the findings of the web-based survey. Researchers, as well as patients experienced in PPI, will be recruited. An interview guide will be developed based on the different elements of the logic framework and will be adapted for researchers and patients. The conduction of focus groups with patients will be discussed and planned together with the participatory research team.

#### Recruitment and procedures

Six focus groups will take place, separately with researchers and patients, with 5 to 7 participants moderated by two members of the project team. Empirical studies have shown that 3 to 6 focus groups will be enough to discover 90% of the themes.^61^ We will recruit participants as outlined. We aim to include a broad range of researchers and patients experienced with PPI in health services research. We will aim for maximum variation in the researcher sample with regard to early-stage and advanced researchers, different fields of expertise (eg, mental health services research) and diversity with regard to individual participants (eg, gender). The patient sample is planned to include diversity with regard to health conditions and associated networks (eg, individual patients vs member/representative in/of patient organisation) as well as sociodemographic factors (eg, gender, age, educational background). The interview guide will be tailored to the participant groups. The core questions concern the context, process, outcomes and impact of PPI. A detailed interview guide will be developed involving the participatory research team.

#### Data analysis

The focus group interviews will be audio-recorded and transcribed verbatim by a professional transcription company. Afterwards, qualitative thematic analysis^62^ will be applied. Relevant passages will be coded using a deductive category system derived from the interview guide. Furthermore, inductive coding to refine the main categories will be applied. There will be two coders, and intercoder reliability will be assessed before the consensus discussions take place within the project team. For the documentation and analysis of the data, the software MAXQDA 2020^63^ will be used.

##### Codesign workshop

The codesign workshop is planned according to the suggestions of Greenhalgh and colleagues.^11^ It will be carried out with approximately 16 researchers, patients and further relevant stakeholders (eg, representatives of the funding bodies or health insurances) in the field of health services research in Germany.

#### Recruitment, procedures and data analysis

Researchers and patients who consented to participate in the previous study parts will be considered; written informed consent will be obtained during each focus group and codesign workshop via paper-pencil. At least four persons from each group should participate in the codesign workshop. Criteria with regard to diversity, only gender and age, will be applied due to the low number of participants in the codesign workshop. Stakeholders should reflect the field of health services research, for example, representatives of the funding bodies or health insurance. The codesign workshop will be a whole day workshop (6 hours). It will start in plenary to present the condensed results of the web-based survey and the themes identified in the focus groups. Participants will have the opportunity to ask questions and to discuss the themes. Following the suggestions,^11^ each participant will be asked to choose up to 10 themes that they think are the most important as indicated by multichoice voting. Participants can indicate their preferences by marking points at the respective themes, which are displayed on flip charts. Accordingly, votes are collected from all participants and will be available in real-time. This information will be available for the following group work aiming at relating the identified themes to the logic model. Participants will work in four groups of approximately four people. Each group should include a mix of researchers, patients and further stakeholders. Each group will be assigned to one of the domains of the logic model (context, process, outcome and impact). Participants can use the presented themes and choose those that reflect the respective domain of the logic model. Afterwards, the preliminary version of the evaluation framework will be presented and discussed in plenary. In particular, themes that have been chosen by more than one group will be discussed and specified. Then, participants will return to the groups to refine their domain based on the discussions. Again, the group will present their domain. The process is repeated if participants bring up further discussion points. It is possible that the evaluation framework will include different domains for researchers and patients. Finally, the framework as a whole will be discussed in plenary and accepted in consensus.

### Phase 2: development of a modular evaluation tool

#### Aim and methods

The development of the modular evaluation tool in the form of a questionnaire is based on Streiner’s^64^ recommendations, including devising and reviewing items. Aspects of validity will also be considered.^65^

##### Item development

In the first step, we generate an item pool based on the existing instruments. In the second step, we will use the themes developed within the analysis of the free-text answers in the web-based survey and focus groups to develop additional items. As numerous instruments have already been developed internationally, as displayed in the review by Boivin *et al*,^21^ we will acknowledge these by linking their items to the developed framework.

#### Procedures and data analysis

Since PPI is a dynamic field and several instruments have not been included^28 29^ in a previous systematic review,^21^ we will first update the review alongside the data collection during the first phase of the project (see figure 1). Afterwards, the items of all identified instruments will be systematically collected. Then, qualitative thematic analysis^62^ will be applied using a deductive category system derived from the components of the consented evaluation framework (see phase 1). Each item will be linked to the content areas. The results will be displayed in a matrix.^64^ There will be two coders, and intercoder reliability will be assessed before consensus discussions will follow. For the documentation and analysis of the data, the computer programme MAXQDA 2020^63^ will be used. Second, items from existing questionnaires for PPI evaluation that match the evaluation framework will undergo a standardised translation procedure, including forwards and backwards translations.^66^ Additionally, the research team will formulate additional items based on the themes derived from the free-text answers of the web-based survey and the focus groups. Ideally, the phrasing of the items is close to the original statements of the participants. This process will result in a comprehensive item pool and the next step includes eliminating redundant or poorly worded items. An iterative process including the participatory research team will be used to refine the items. Afterwards, scaling will be specified. Finally, a preliminary version that undergoes cognitive pretesting will be defined. With regard to the proposed modular character of the evaluation tool, separate modules can be developed for researchers and patients.

##### Cognitive pretests

#### Procedures and data analysis

Cognitive pretests will use the ‘Think Aloud’ technique.^67^ We will invite 5 researchers and 5 patients who have already participated in the previous study phases to the first round; consent will be obtained on-site using paper-pencil forms. The researchers and patients will be asked to verbalise their thoughts that lead them to the answer while filling out their questionnaires. We plan to conduct cognitive pretests in person. Therefore, we will primarily recruit patients locally. The ‘Think Aloud’ will be recorded in writing and evaluated. Using the data from the cognitive pretests, the researchers and the participatory research team will discuss and decide on revisions. The decisions will be reached by consensus. The revised items will be presented in a second round of cognitive pretests involving another 5 researchers and 5 patients. After a further revision, the pretested and revised modular evaluation tool will undergo qualitative review.

##### Qualitative review

#### Procedures and data analysis

An online qualitative review will be conducted to investigate the face validity of the developed items. Researchers, patients and stakeholders who participated in the codesign workshop will be invited for the qualitative review. A web-based survey including all items will be administered using REDCap; informed consent will be obtained online.^58^ Participants will judge each item with regard to its relevance on a 4-point scale (1: not relevant, 2: somewhat relevant, 3: quite relevant, 4: highly relevant). They will also be asked whether any important questions are missing. To ensure that all items are relevant and reflect the evaluation framework, the Content Validity Index (CVI) will be calculated.^68^ The CVI is computed as the number of experts giving a rating of ‘very relevant’ for each item divided by the total number of experts. Values range from 0 to 1 where CVI >0.79, the item is relevant; between 0.70 and 0.79, the item needs revisions and if the value is below 0.70, the item is eliminated. Nevertheless, there should be at least three items per domain. Based on the scores, a revision will be made.

### Phase 3: piloting a modular evaluation tool

#### Aim and methods

The pilot study is intended to provide information on the reliability and validity of the developed modular evaluation tool. We will consider the relevant literature on the quality criteria for health outcome measurements.^65 69^ With regard to reliability, we will focus on internal consistency and retest reliability, as there are no measurement standards for PPI evaluation tools. Additionally, we will account for the additional aspects of construct validity: factorial validity and convergent validity.

##### Web-based pilot study

#### Recruitment and procedures

Researchers and patients will be recruited by updating identifying the principal investigators of ongoing publicly funded health services research. Additionally, snowball sampling and sampling through personal knowledge will be applied. Researchers and patients will be invited to take part in web-based pilot testing of the modular evaluation tool. They will receive emails and individualised links. Reminders will be sent to improve the response rates.^57^ Participants are eligible when they are involved in a currently ongoing health research project that implements PPI. At the end of each survey, participants can also generate a code for specific ongoing projects and send links to the web-based pilot study to identify other project members. The code can be used to merge evaluations on specific projects. Moreover, participants can choose whether they would like to receive a score sheet after closure of the pilot study.

Overall, the pilot study is intended to collect a total of at least 200 responses. Modules that can be answered by researchers or patients only should be answered by at least 100 participants. This will constitute an appropriate sample size providing insights into psychometric testing.^70^ A randomly chosen subsample of n=50 will be invited to fill in the core modules a second time after approximately 1 week. REDCap^58^ will be used to implement the web-based survey. Informed consent will be obtained online.

The survey will include the items from the developed modular evaluation tool items as well as the PPEET^27^ to establish convergent validity. The PPEET has previously been used for validation studies,^29^ and an authorised German version of the PPEET exists. Participating researchers and patients will also be asked to provide information on individual characteristics, such as age and gender, as well as seniority for researchers and patients’ health condition with lived experience for patients, respectively.

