### Data handling

New data will be generated in the empirical parts of the proposed project (survey, interviews). Researchers and patients will provide quantitative (eg, ratings) as well as qualitative data (eg, text, speech) in the web-based surveys, focus groups and co-design workshops. The web-based surveys conducted in phase 1 and phase 3, along with the qualitative review, will use the REDCap. REDCap supports data collection in accordance with the law (ie, DGSVO), protecting the privacy of respondents (eg, secure infrastructure, no cookies, no IP addresses in log files). For transcription of the focus groups, audio recordings will be uploaded to a secure and encrypted network and handled, ensuring data protection regulations. Quality checks of the transcripts will be performed by the interviewers and, if agreed on, by the interviewees. Audio recordings will be deleted after transcription, and the transcripts will be anonymised. Protocols will be made available for those who took part in the workshops or cognitive debriefings. This allows a quality check.

Informed consent for participation in the online surveys, focus groups, co-design workshops, cognitive debriefing and qualitative review will be obtained. The project team will store all data on a secure and encrypted network drive, with access to project team members. Declarations of consent and transcripts or protocols will be archived separately for 10 years before deletion. When compiling the results, no information will be published that could allow conclusions to be drawn about individual persons.

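### The retest subsample of 50 is drawn at random with no split by role, so the number of patients in it is left to chance and to the pilot's mix

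*Protocol article*

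**What the plan says.** All of this stands in the protocol article under Phase 3, Web-based pilot study, unless another place is named.

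- **Retest (Recruitment and procedures).** "A randomly chosen subsample of n=50 will be invited to fill in the core modules a second time after approximately 1 week". No strata, no number per role and no target for completed pairs are given.
- **Pilot size (same section).** The overall target is 200 responses or more. Material meant for one role has its own floor: "Modules that can be answered by researchers or patients only should be answered by at least 100 participants". Both are lower limits, and both concern the pilot, not the retest.
- **Analysis (Data analysis).** Test-retest reliability is to be assessed by correlations. No analysis by role is stated. Further aspects of reliability testing are left until the evaluation framework is agreed.
- **Purpose.** The Objectives ask whether the tool gives stable and consistent results. The Abstract describes a tool with modules for researchers and for patients, and Phase 2 (Item development) allows separate modules for the two. The Phase 3 aim names retest reliability as one of the two reliability properties to be studied.

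**The concern.** The two roles answer from different positions in a project, and the plan otherwise treats them separately: possibly separate modules, and a separate minimum for role-only modules. The retest is the only source of evidence on stability over time, and its composition is not controlled. A random draw follows the mix of the pilot sample. Since the pilot targets are floors, a pilot with many more researchers than patients would meet the plan, and the retest would then hold few patients.

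At stake is whether the retest can say anything useful about patients' answers. A pooled coefficient dominated by one role could be read as evidence for both. Because 50 people are invited rather than completed, the number of pairs per role will be lower still if some do not reply.

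**Working it through.** **Inputs from the document.** Retest invitations: n = 50. Pilot minimum: 200 in total, 100 per role-only module. The two figures agree: 100 + 100 = 200. The article gives no derivation for the 50, so there is no figure to reproduce for it.

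**Assumptions.** (a) The draw is unstratified, which is the plain reading of a random choice with no strata named. (b) Every pilot participant can be drawn. (c) The mixes 150 + 100 and 200 + 100 are illustrations; the article gives no such ratio. (d) The retest coefficient is 0.75.

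**Step 1: number of patients in the draw.** With R researchers, P patients and N = R + P, the number of patients among 50 drawn without replacement is hypergeometric:

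- mean = 50 × P/N
- variance = 50 × (P/N) × (R/N) × (N − 50)/(N − 1)

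For 100 + 100: mean = 50 × 100/200 = 25; variance = 50 × 0.5 × 0.5 × 150/199 = 9.42; SD = 3.07.

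| Pilot (researchers + patients) | Expected patients | Central 95% range | P(20 or fewer patients) |
|---|---|---|---|
| 100 + 100 | 25.0 | 19–31 | 7% |
| 150 + 100 (assumed) | 50 × 100/250 = 20.0 | 14–26 | 57% |
| 200 + 100 (assumed) | 50 × 100/300 = 16.7 | 11–23 | 90% |

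In the equal pilot, researchers face the same 7%. The two events cannot both happen when 50 are drawn, so the chance that either role has 20 or fewer is 2 × 7.06% = 14%.

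**Step 2: what the number of pairs means for precision.** Fisher's z: z = atanh(0.75) = 0.973; limits = tanh(0.973 ± 1.96/√(n − 3)).

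| Pairs | 1.96/√(n − 3) | 95% interval |
|---|---|---|
| 25 | 0.418 | 0.50–0.88 |
| 20 | 0.475 | 0.46–0.89 |
| 17 | 0.524 | 0.42–0.90 |

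These are counts of completed pairs. Non-response among the 50 invited would reduce them further; the article gives no rate.

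**The case against.** The strongest reply is that no role-specific retest result is planned, so there is no role target to miss. The Objectives ask about the tool, the analysis is a correlation without a split, the retest covers core modules, and further reliability details are deferred. This stands in part: the plan contains no error of arithmetic and no contradiction here. It does not remove the point, because a pooled coefficient from an uncontrolled mix still has to support a tool meant for both roles.

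A second reply is that the effect is small. In an equal pilot the chance of too few patients is 7%, and moving from 25 to 20 pairs widens the interval only from 0.50–0.88 to 0.46–0.89. This stands. The larger effects need a researcher-heavy pilot, which the minimums permit but the article does not predict.

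A reader might also infer more from how people enter the pilot. Invited people are sent personal links ("They will receive emails and individualised links"), while "participants can also generate a code for specific ongoing projects and send links to the web-based pilot study to identify other project members", and the code works at project level ("The code can be used to merge evaluations on specific projects"). From this one could conclude that people who arrive by a forwarded link have no individual link, are mainly patients, cannot be reached for the retest and cannot be checked for repeat entry. The article does not show this:

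- It does not say what kind of link is forwarded.
- Other project members include researchers, and patients can also be invited directly or through personal knowledge.
- Inviting people again after a week already implies that contact details are held.
- The remark "no cookies, no IP addresses in log files" (Data handling) describes privacy features of the survey software and does not rule out an email field or a person code.

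Such operational detail may be in the full protocol, so it is no part of this point.

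**Conclusion.** The point holds as a modest design improvement. The article fixes a random retest subsample of 50 without a role split, and nothing else in it protects the number of patients (or of researchers) in that subsample.

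With equal roles the risk is small: 7% for 20 or fewer patients, 14% for either role. It becomes likely only if the pilot recruits clearly more researchers than patients: 57% at 150 + 100 and 90% at 200 + 100. These figures rest on an unstratified draw, on everyone being available to be drawn, and, beyond the equal case, on assumed mixes. The loss of precision rests on an assumed coefficient of 0.75. Even 25 pairs per role give a wide interval, so stratifying guards against a poor split but does not make the by-role estimates precise.

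**What to change.** In Phase 3, Web-based pilot study, Recruitment and procedures, state that the retest subsample is drawn at random within role: 25 researchers and 25 patients. Under Data analysis, state that the retest coefficient is reported by role as well as overall, each with a 95% interval, and that the by-role intervals are expected to be wide (about 0.50 to 0.88 at a coefficient of 0.75 with 25 complete pairs).

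The cost is two sentences. The number invited stays at 50, and role is known from the module that each person answers. The equal split is a proposal; the article sets no such target.
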